### Sample size calculation

Sample size calculations took into consideration the cluster randomisation design by incorporating the design effect into the calculation. The design effect was calculated based on a cluster size of 20 and the intracluster correlation coefficient (ICC) using the formula: Design Effect = 1 + (within cluster sample size −1) x ICC. In the absence of ICCs for the outcome measures, available population standard deviations were used to calculate the variances and the ICC using the formula: ICC = variance between cluster/(variance between cluster + variance within cluster). In this study, there were two primary outcome measures, calcium intake and physical activity. Sample size calculations were carried out for both measures. Calculations were based on α = 0.05 and β = 0.1. Table 
1 shows the parameters used for calculating the number of clusters and the total number of participants. The study deliberately planned to over recruit within clusters to factor in a 30% attrition rate.

**Table 1 T1:** Summary of parameters used in the sample size calculation

**Outcome measures and mediators**	**Effect size**	**ICC used in sample size calculation**	**Standard deviation used in sample size calculation**	**Design effect**	**Number of clusters**	**Total subjects to be recruited**	
						**Before factoring in 30%****attrition**	**After factoring in 30%****attrition**
Calcium intake (milligrams per day)	250 milligrams	0.5*	290 milligrams***	10.5	14.7	294	480
Physical activity duration (minutes per week)	60 minutes	0.05**	150 minutes****	1.95	13	255	420

*Calculated using standard deviation from National Nutrition Survey 1998 and based on conservative estimates of inter- and intra-cluster variance
[23].

**Based on estimates from published studies
[30,31].

***Estimate from National Nutrition Survey 1998
[32].

****Based on estimates from published studies
[33,34].

The number of clusters required was different for each outcome measure, so the study was based on the highest number of clusters required, which was that for calcium intake (14.7). This was rounded up to 16 to ensure equal cluster numbers in both arms of this study.

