### Data collection

Data for the two outcome measures, calcium intake and physical activity, were collected at three time points for both study arms. The mediators in this study, self-efficacy scores for calcium intake and physical activity, were also collected at the same time points. Demographic and lifestyle information were collected at baseline.

The three data collection points were:

•Baseline: four weeks before the intervention

•Four weeks after the intervention workshops (for the intervention group) were completed

•Six months after the first post-intervention data collection was completed

Data collection for both the intervention and control arms took place during similar periods at every time point. Figure 
2 provides an overview of the timeline for data collection.

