### Proposed data analysis

All analyses will follow intention-to-treat principles when comparing intervention and control arms
[46]. Data from the second follow up will be analysed to compare short-term changes after the intervention. Data from the third follow up will be analysed to assess sustainability of any observed changes. The primary dependent variables are calcium intake (milligrams per day), moderate to vigorous intensity load-bearing physical activity level (duration in minutes per week).

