### Cluster level analysis that adjusts for individual covariates and baseline measures

The main hypotheses will be tested using cluster-level analyses. This approach adheres to the recommendation of the 2004 Consort Statement for cluster randomised trials to fully account for the clustering effect
[46,47] and is recommended for studies with small number of clusters
[47,48]. Individual-level analysis using multi-level/mixed models was considered, but this study does not have the required cluster numbers for multilevel modelling as recommended by some analysts (minimum recommended is 15 cluster per arm)
[47].

This study will use the two-stage adjusted analysis based on cluster summaries developed by Hayes and Moulten (2009, pp182-184)
[47]. In stage one, SPSS linear regression will be run to generate an unstandardised residual for each subject (the difference between the observed value and the fitted value from the model for each individual participant). Baseline calcium value for each subject will be controlled for in the linear regression model. Other variables that were identified as potential confounders will also be included in the model as factors or covariates. This step incorporates repeated measures into the analysis and generates the covariate-adjusted residuals for each individual.

Cluster summaries for the covariate-adjusted residuals are then generated using SPSS descriptive statistics. These summaries are for stage two of the analysis, which is the cluster level analysis. The cluster means of the residuals are then compared in a cluster level analysis using a weighted *t*-test, with weighting based on cluster size (number of participants per cluster).

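### The stage-one model serves both primary outcomes but names only baseline calcium, so adjustment of physical activity for its own baseline is not fixed

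*Protocol article*

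**What the plan says.** The protocol article makes two outcomes primary. Under Sample size calculation: "In this study, there were two primary outcome measures, calcium intake and physical activity". Under Proposed data analysis, the activity variable is "moderate to vigorous intensity load-bearing physical activity level (duration in minutes per week").

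Both were measured before and after the intervention. Under Data collection: "Data for the two outcome measures, calcium intake and physical activity, were collected at three time points for both study arms". The first of those time points is baseline.

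The analysis section is headed "Cluster level analysis that adjusts for individual covariates and baseline measures". It states that "The main hypotheses will be tested using cluster-level analyses" and then describes a single stage-one linear regression. On covariates it says two things:

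- The one baseline value it names: "Baseline calcium value for each subject will be controlled for in the linear regression model"
- A general clause that lists no variables: "Other variables that were identified as potential confounders will also be included in the model as factors or covariates"

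It adds: "This step incorporates repeated measures into the analysis and generates the covariate-adjusted residuals for each individual". The cluster means of the residuals then go into a weighted *t*-test. Baseline activity is not named as a covariate anywhere in the article.

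**The concern.** The article does specify a baseline covariate, and the one it specifies fits only one of the two primary outcomes. Followed to the letter, the activity model must carry baseline calcium, which has little evident reason to predict activity minutes. It need not carry baseline activity, which is likely to be the strongest available predictor.

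The clause on potential confounders could bring baseline activity in, but it lists no variables and gives no rule for choosing them. Calcium's own baseline is therefore guaranteed, while activity's is discretionary. If the choice were made after the data were seen, adjustment of a primary outcome for its baseline would become an analyst's option.

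With eight workplaces per arm, and no stratification or matching described under Cluster randomisation process, a sizeable chance difference in baseline activity is quite possible. Own-baseline adjustment would account for it and would also reduce residual variance.

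**Working it through.** **1. What the text fixes for each outcome**

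| | Calcium intake | Activity minutes |
|---|---|---|
| Primary outcome | yes | yes |
| Baseline collected | yes | yes |
| Covered by the stage-one model | yes | yes |
| Own baseline named as covariate | yes | no |
| Own baseline could enter as a potential confounder | not needed | yes, if selected |

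The heading (baseline measures, plural) and the sentence on repeated measures fit an own-baseline rule for both outcomes. The covariate sentence delivers it for calcium only.

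**2. Inputs for the size** (Sample size calculation, Table 1, and the abstract): effect 60 min/week, SD 150, ICC 0.05, cluster size 20, 16 clusters (8 per arm), α = 0.05 (taken as two-sided), β = 0.1. The baseline to follow-up correlation *r* is **not** in the document; 0.3, 0.5 and 0.7 are assumed.

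**3. The plan's own figure.**

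- Design effect = 1 + 19 × 0.05 = 1.95.
- n = 2 × (150/60)² × (1.960 + 1.282)² = 131.3.
- 131.3 × 1.95 = 256, or 12.8 clusters of 20.

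Table 1 gives 255 and 13, so the figure reproduces. It is a per-arm number, as the article itself acknowledges when it reports that the doubling step was missed. No baseline adjustment enters this calculation.

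**4. Standard error without baseline adjustment** (equal clusters of 20):

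SE = 150 × √[2 × (0.05 + 0.95/20) / 8] = 150 × √0.024375 = 23.4 min/week.

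**5. Power for 60 min/week.** Suppose own-baseline adjustment removes a fraction *r*² of the variance at both individual and cluster level. Then the adjusted SE is 23.4 × √(1 − *r*²). Power is from the noncentral *t* with 14 df (two-sided critical value 2.145).

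| Assumed *r* | SE (min) | 60/SE | Power, *t* 14 df | Power, normal approximation |
|---|---|---|---|---|
| no adjustment | 23.4 | 2.56 | 66% | 73% |
| 0.3 | 22.3 | 2.69 | 70% | 77% |
| 0.5 | 20.3 | 2.96 | 79% | 84% |
| 0.7 | 16.7 | 3.59 | 92% | 95% |

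**6. The same point seen conditionally.** If SD and ICC are the same at baseline, a chance baseline difference of one SE (23.4 min) moves an unadjusted follow-up difference by *r* × 23.4, about 7, 12 or 16 min. This is not an additional harm. It is part of the variation already in the 23.4-minute SE, and the reduction in step 5 comes from accounting for it.

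**The case against.** A reader might infer that the model adjusts for calcium alone, or that activity will not be adjusted for its own baseline. The text supports neither. Other potential confounders are to be included, and baseline activity could be among them. No sentence excludes it. The heading and the repeated-measures sentence suggest that each outcome's own baseline was meant, with calcium, the outcome that set the number of clusters, written as the worked case. On that reading the repeated-measures sentence is a sign of intent; it should not be treated as a second error.

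It can also be said that a condensed article leaves covariate lists to an analysis plan. That holds for the unnamed confounders, and their absence is not criticised here. It does not fully answer the point, because the article does state a baseline rule and states it for one outcome only.

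On size, three objections stand:

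- Chance imbalance under randomisation does not bias the estimator.
- The gain depends on an assumed correlation acting at both levels; at 0.3 it is only about four percentage points.
- The low starting power reflects the disclosed sample-size error and owes nothing to the choice of covariates.

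**Conclusion.** The point holds as a badly fixed rule. The stage-one model covers both primary outcomes, names the baseline of one, and leaves the baseline of the other to an unspecified selection. Probable intent is a reason to write the rule down. It does not show that the planned analysis is wrong.

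The benefit of fixing it is precision and protection from chance baseline imbalance: power for 60 min/week of about 70% to 92%, against about 66% with no baseline adjustment. That range rests on the plan's SD, ICC and cluster numbers, equal cluster sizes, and an assumed correlation of 0.3 to 0.7 at both levels, so it is illustrative only. The 66% is a reference case; the analysis finally run may well include baseline activity. None of the article's stated figures changes. This is a free improvement.

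**What to change.** Replace the sentence on baseline calcium with:

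> *Each outcome is adjusted for its own baseline value (baseline calcium in the calcium model, baseline moderate-to-vigorous load-bearing activity minutes in the activity model) at both follow-ups.*

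The cost is one sentence. Baseline activity is already collected in both arms, and the design, sample size and two-stage method stay as they are.

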### Process to outcome analysis

Analysis will also test for the mediating effects of self-efficacy (SE) scores on calcium intake and physical activity measures. The relationships between the SE scores and the outcome measures will be examined at baseline and each follow up by exploring if changes in the self-efficacy scores are predictive of changes in the outcome measures in this cohort. The intervention theory and design assumes self-efficacy to be a strong mediator of outcome and this assumption will be tested and discussed.

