### Aims

The overall aim of this study was to determine the efficacy of a tailored and self-efficacy focussed workplace-based intervention compared with standard care (print resources) in increasing the calcium intake and physical activity level of women with sedentary occupations.

The specific objectives were:

1. To test the hypothesis that a tailored workplace based intervention incorporating specific behavioural strategies for calcium intake and physical activity is more efficacious than standard care (simple print resource distribution) in increasing the calcium intake and physical activity levels.

2. To explore the relationship between self-efficacy scores for calcium intake and physical activity with actual calcium intake and physical activity levels to determine the extent to which self-efficacy mediates intervention-associated changes in calcium intake and physical activity.

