There was an error in the final step of this study's sample size calculations. The calculation did not double the sample size calculation that yielded the number of required subjects per arm (for this two-arm study). The sample size calculation, however, was very conservative with the ICC estimates and the study was expected to be overpowered despite the omission of this step. This study still has 90% power to detect 355 milligrams increase in calcium intake and 85 minutes increase in moderate to vigorous intensity physical activity with 16 clusters of 20 participants per cluster.

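### The mediation analysis, as described, tests only whether self-efficacy change predicts outcome change, so it cannot give the extent of mediation that objective 2 asks for and can indicate mediation falsely

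*Protocol article*

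**What the plan says.** Objective 2, under Aims in the protocol article, is exploratory in tone but has a quantitative target: "to determine the extent to which self-efficacy mediates intervention-associated changes in calcium intake and physical activity".

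Process to outcome analysis then gives three things:

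- **Purpose:** "Analysis will also test for the mediating effects of self-efficacy (SE) scores on calcium intake and physical activity measures".
- **Method:** the relationships are examined at baseline and each follow-up by "exploring if changes in the self-efficacy scores are predictive of changes in the outcome measures in this cohort".
- **Inference:** "The intervention theory and design assumes self-efficacy to be a strong mediator of outcome and this assumption will be tested and discussed".

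Two other places bear on the point. Data collection says that the mediators, "self-efficacy scores for calcium intake and physical activity, were also collected at the same time points" as the outcomes. The section on cluster-level analysis says "The main hypotheses will be tested using cluster-level analyses", and nothing in the mediation section takes up clustering either way.

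**The concern.** The extent of mediation is the part of the arm effect that passes through self-efficacy. It needs two links, arm to self-efficacy and self-efficacy to outcome given arm, and an estimate that combines them. The section describes one association, between two change scores. However strong it turns out to be, it does not say how much of the intervention effect runs through self-efficacy.

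The association can also arise without mediation, in three ways:

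- **Separate routes.** The workshops aim to raise self-efficacy and also use food tasting, label reading and exercise sampling. If these act on behaviour directly, both variables move with arm and their changes correlate across arms.
- **A shared cause.** A participant who is more motivated, or less busy, may improve on both.
- **Clustering.** If participants are treated as independent, colleagues moving together can produce apparent associations.

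Self-efficacy and outcomes are measured at the same visits, so same-visit changes would not settle direction either: success in eating more calcium may raise confidence. Self-efficacy is the theoretical basis of the intervention, so a false confirmation would matter for how the trial is read.

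**Working it through.** **1. Target against method**

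| Needed for objective 2 | Named in the mediation section? |
|---|---|
| Arm effect on self-efficacy | No |
| Self-efficacy to outcome, given arm | Association of changes only; no arm term |
| Indirect effect | No |
| Adjustment for shared causes | No |
| Allowance for workplaces | No |

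The plan gives no figure for this analysis, so there is none to reproduce.

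**2. Inputs for an illustration**

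- Design: "with 16 clusters of 20 participants per cluster", so n = 320, with eight workplaces per arm.
- Significance level: "Calculations were based on α = 0.05 and β = 0.1". Sidedness is not stated; two-sided 5% is assumed.
- Calcium shift: d = 250/290 = 0.86 SD (Table 1). This treats the tabulated 290 mg as the SD of change.
- Physical activity shift: d = 60/150 = 0.40 SD (Table 1), with the same treatment of the SD.
- Assumed, not in the document: arms pooled; workshops raise self-efficacy by a = 0.5 to 1.0 SD; self-efficacy has no effect on the outcome.

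**3. Closed form, independent participants (ICC 0)**

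With equal arms and unit within-arm SD, the correlation of the changes is

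r = 0.25·a·d / √[(1 + a²/4)(1 + d²/4)].

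The chance of p < 0.05 follows from Fisher's z, atanh(r)·√317, against 1.96.

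- Calcium, a = 0.5: r = 0.25 × 0.5 × 0.862 / √(1.0625 × 1.186) = 0.096; z = 1.71; about 40%.
- Calcium, a = 1.0: r = 0.177; z = 3.19; about 89%.
- Physical activity, a = 0.5: r = 0.25 × 0.5 × 0.40 / √(1.0625 × 1.04) = 0.048; z = 0.85; about 14%.
- Physical activity, a = 1.0: r = 0.088; z = 1.57; about 35%.

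**4. Simulation with workplaces (no true mediation)**

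- Calcium, ICC 0 to 0.3: 41–46% significant at a = 0.5 and 76–90% at a = 1.0.
- Physical activity, ICC 0.05 as in Table 1: 14.6% at a = 0.5 and 37.4% at a = 1.0.
- Smaller self-efficacy shifts of 0.2 and 0.3 SD, ICC 0.05: 12.6% and 20.5% for calcium; 7.9% and 8.9% for physical activity.
- Arm moves neither variable, or only one of them by 0.5 SD; ICC 0.05, no shared cause: 5.4–6.6%.
- Shared-cause correlation of 0.2 or 0.3, no arm effects, ICC 0.05: 92% and 100%.
- ICC 0.5 (the calcium planning value) on both variables, no effect of any kind, clustering ignored: 40%.

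**5. Would a two-path test do better?**

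A joint test requires both an arm effect on self-efficacy (cluster-level t-test) and an arm-adjusted self-efficacy-to-outcome association. At ICC 0.05 without a shared cause, its false-positive rate is 0.2–5.6%, in scenarios where the pooled correlation gives 5.4–68.9%.

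It does not protect against a shared cause. With residual correlation 0.3 and 0.5 SD arm effects on both variables, it is falsely positive in 84% of runs. An indirect-effect interval from resampling whole workplaces (400 runs, baselines omitted, self-efficacy shift 0.5 SD, residual correlation 0.2) fails in 94% at ICC 0 and 89% at ICC 0.05. Without a shared cause it still excludes zero in 8% and 11.5%, so it is somewhat too narrow with eight workplaces per arm.

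**The case against.** The best defence is that this is a condensed article. The section opens with a general commitment to test mediation, and the sentence on change scores may describe one component of it. Model terms, the indirect-effect estimator and the standard errors are details that a fuller plan commonly holds. The authors also treat self-efficacy as a clustered variable, since Limitations promises its observed ICC.

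Much of this stands. A reader might infer that the arms are pooled, that only same-visit changes are related, and that standard errors ignore workplaces. The document states none of these. The reference to the cohort is the only wording that points to pooling, and examining each follow-up does not exclude a lagged analysis. A reader might also infer that the analysis will find mediation where there is none. That is too strong: the error rate stays near 5% when the arm does not move both variables, no shared cause exists and clustering is small. The high calcium figures also rest on assumed self-efficacy shifts, and the physical activity figures are much lower.

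What does not stand is treating the whole point as missing detail. The section states a purpose, a method and an inference, and the stated method does not support the inference. An association within arms, or with clustered standard errors, would still not give an indirect effect.

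**Conclusion.** The point holds in this form: the method described covers one link, cannot answer objective 2, and can indicate mediation falsely. The risk from separate routes is greatest when the workshops succeed on both self-efficacy and behaviour, which is what the trial expects.

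The size is illustrative. About 40–90% false positives for calcium and about 14–37% for physical activity rest on pooled arms, no true mediation, self-efficacy shifts of 0.5 to 1.0 SD, the planned effects being achieved, and the tabulated SDs serving as SDs of change. The conclusion that the stated method yields no extent of mediation rests on none of these assumptions.

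The change should be made, but it concerns a secondary, exploratory objective. The primary comparisons are unaffected.

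**What to change.** For each outcome, state the mediation model as follows:

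1. **Arm to self-efficacy.** Estimate the arm effect on 4-week self-efficacy with the two-stage cluster method, adjusting for baseline self-efficacy.
2. **Self-efficacy to outcome.** Regress the final-visit outcome on arm, 4-week self-efficacy, baseline self-efficacy, baseline outcome, and those baseline covariates already collected that may confound the self-efficacy–outcome relation.
3. **Indirect effect.** Report it with an interval that respects workplaces, by resampling whole workplaces within arm, and note that it may be somewhat too narrow with eight per arm.
4. **Sensitivity analysis.** Show how strong an unmeasured self-efficacy–outcome confounder would have to be to remove the indirect effect. This step is essential, because steps 1 to 3 alone fail under a shared cause.

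Report the 4-week version of the model as secondary, because it has no time order. Keep the change-on-change associations, within arm, as descriptive only.

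The cost is extra programming on data already collected. With 16 workplaces the interval for the indirect effect will be wide, and the report should say so.

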## Discussion

This study design was developed in response to the need for a well-designed population-based intervention to target osteoporosis prevention behaviours. Although dietary and physical activity behaviour interventions have been extensively researched, limited investigation has been carried out to study the specific domains of these two behaviours relevant to bone health and osteoporosis prevention.

